### Sample size calculations

Primary outcomes will be the 12-month change in (i) overall average knee pain severity over the last week measured using an 11-point numeric rating scale; and (ii) medial tibial cartilage volume from MRI expressed as a percentage. The minimum clinically important difference to be detected in OA trials is a change in pain of 1.8 units (out of 10) [24]. Using control group data from our 12-month RCT in people with mild to moderate knee OA, we assume a between-participant standard deviation (SD) of change in pain of 2.4 and baseline to 12-month correlation in scores of 0.29 [30]. We wish to find a 40% reduction in the amount of medial tibial cartilage volume loss with PRP. Based on our data [40], slowing the rate of cartilage loss by this amount could delay the need for knee replacement. We anticipate the control group to lose 2.8% (SD 3.5%) of medial tibial cartilage volume in 12-months [30], with a conservative baseline to 12-month correlation in scores of 0.50. These assumptions, together with an analysis of covariance adjusted for baseline scores, indicate that 115 participants per arm will have 80% power to detect a 40% reduction in loss of cartilage volume with a two-sided significance level of 0.05. With this number of participants, we also have > 99% power to detect the minimum clinically important difference in pain. Allowing for 20% loss to follow-up, we will recruit 144 participants per arm - total 288 participants.

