### Outcome measures

Study outcome measures are presented in Table 1. Our two primary outcome measures are 12-month change in overall average knee pain severity and medial tibial cartilage volume:i)*Average overall knee pain severity*: this will be measured at baseline, 2, 6, 9 and 12 months using an 11-point numeric rating scale (NRS) with terminal descriptors ‘no pain’ (score 0) and ‘worst pain possible’ (score 10). This was chosen because it has well-established clinimetric properties in knee OA and established minimal clinically important differences [24], and is a recommended measure for knee OA RCTs from the Osteoarthritis Research Society International [25].ii)*Medial tibial cartilage volume*: an MRI scan of the study knee will be performed at baseline and 12 months using a 3 T whole body system with a dedicated extremity coil and a T1-weighted fat-suppressed 3D gradient recall acquisition sequence (Additional file 1). Medial tibial cartilage volume will be measured by manually drawing disarticulation contours around the cartilage edges, section by section. To reduce measurement error and bias, one person will measure each participant’s paired set of images, blinded to time sequence and treatment allocation. Regular quality review will occur in 20% of images by a second reader. Our coefficients of variation for these measures are 2.3–2.4% [26].

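### The cartilage sample size calls a correlation of 0.50 conservative, but with the SD of change fixed it is a favourable choice: 80% power is not a lower bound, and power falls to 68% at worst

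*Protocol article*

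**What the plan says.** All the planning figures are in the protocol article under Sample size calculations. For the structural primary outcome:

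- Control-group loss and its spread: "We anticipate the control group to lose 2.8% (SD 3.5%) of medial tibial cartilage volume in 12-months".
- Target effect: "We wish to find a 40% reduction in the amount of medial tibial cartilage volume loss with PRP".
- Correlation: "with a conservative baseline to 12-month correlation in scores of 0.50".
- Planned analysis for the calculation: "together with an analysis of covariance adjusted for baseline scores".
- Result: these assumptions "indicate that 115 participants per arm will have 80% power to detect a 40% reduction in loss of cartilage volume", at two-sided 0.05. Allowing for 20% loss to follow-up gives 144 per arm and 288 in total.

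The pain outcome is set up in the same way, with an SD of change (2.4) paired with a correlation between baseline and 12-month scores (0.29). Its power is given as above 99%, so cartilage volume sets the trial size.

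Under Outcome measures, the article reports the reading precision of cartilage volume: "Our coefficients of variation for these measures are 2.3–2.4" per cent.

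**The concern.** Calling a planning value conservative tells the reader that the truth is probably more favourable, so that power is at least the stated figure. For a correlation between baseline and follow-up, that holds when the SD in the calculation is the SD of a score at one visit, because a higher correlation then removes more variance. It is reversed when the SD is that of the change. A high correlation is then already reflected in a small SD of change, and baseline adjustment has little left to gain.

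Here the SD is attached to the 12-month loss. If the true correlation exceeds 0.50, as the label suggests, power for cartilage volume is below 80%. A null structural result could then be read as coming from a trial with at least 80% power when the chance of missing the target effect was larger, up to about one in three (32%).

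**Working it through.** **Inputs (Sample size calculations).** Control loss 2.8%, SD of change 3.5%, 40% relative reduction, ρ = 0.50, two-sided α = 0.05, 80% power, 1:1 allocation, 20% loss to follow-up.

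**Difference to detect.** 0.40 × 2.8 = 1.12 percentage points.

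**Reproducing the stated figure.** n per arm = 2 × (1.96 + 0.8416)² × 3.5² × f / 1.12², where f is the variance factor for baseline adjustment.

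- If 3.5 is the SD of a score, f = 1 − ρ² = 1 − 0.25 = 0.75.
- If 3.5 is the SD of change, with equal variances at the two visits, f = (1 + ρ)/2 = 1.5/2 = 0.75.

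Both give n = 114.97, so 115 per arm, and 115/0.8 = 143.75, so 144. The plan's figures reproduce. Because the two factors coincide at exactly 0.50, the match does not show which formula was used. They move in opposite directions on either side of 0.50.

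**Which factor applies.** The 3.5% describes the loss over 12 months, and the correlation is between scores. That is the second case, f = (1 + ρ)/2.

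**Power with 115 evaluable per arm.** Power = Φ(1.12 / [3.5 × √f × √(2/115)] − 1.96). At ρ = 0.50 the standard error is 3.5 × 0.8660 × 0.1319 = 0.400, so power is Φ(2.80 − 1.96) = 80.0%. With no gain (f = 1) the standard error is 0.462, so power is Φ(2.43 − 1.96) = 68.0%.

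| ρ | f | Power, 115 per arm | n per arm for 80% power |
|---|---|---|---|
| 0.50 | 0.75 | 80.0% | 115 |
| 0.70 | 0.85 | 74.9% | 131 |
| 0.80 | 0.90 | 72.5% | 138 |
| 0.90 | 0.95 | 70.2% | 146 |
| 0.95 | 0.975 | 69.1% | 150 |
| no gain | 1 | 68.0% | 154 |

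A simulated ANCOVA with 115 per arm (4,000 runs each) gave 79.7% at ρ = 0.50 and 67.3% at ρ = 0.95, broadly in line with the formula.

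**Reduction detectable with 80% power at 115 per arm.** 2.8016 × 3.5 × √f × √(2/115) / 2.8:

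- f = 0.75: 1.12/2.8 = 40%.
- f = 0.95: 1.26/2.8 = 45%.
- f = 1: 1.29/2.8 = 46%.

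**If nobody is lost (144 per arm).** Power is 88.0% at ρ = 0.50, 79.6% at 0.90, 78.5% at 0.95 and 77.5% with no gain.

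**Is 0.50 plausible on the article's own figures?** With equal variances, SD of change = SD of volume × √(2(1 − ρ)). At ρ = 0.50 this gives a between-person SD of volume of 3.5/√1 = 3.5% of the mean. The reading CV is 2.3–2.4%. If reading errors are independent between images, the true between-person SD is √(3.5² − 2.35²) ≈ 2.6%. That is narrow for a measure whose models the article plans to adjust for gender, BMI and tibial plateau area. Assumed between-person SDs of 5%, 10% and 20% give ρ = 1 − 3.5²/(2 × SD²) = 0.755, 0.939 and 0.985, and power 73.6%, 69.3% and 68.3%. A correlation of 0.90 corresponds to an SD of about 7.8%.

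**The case against.** **No stated figure is miscalculated.** This stands. From the article's inputs, 115, 80% and 144 are all correct. What is wrong is the label, and with it the implied claim that 80% is a floor.

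**A reader might infer that the true power is about 68–70%.** The documents do not support that as a fact. It needs a correlation of 0.90 or more, and the article reports neither an observed correlation nor a between-person SD; the source of the SD of change is a cited study that is not at hand. The reading CV makes 0.50 look low but does not yield 0.90: an assumed between-person SD of 5% gives 0.755. One person also reads each participant's paired images, so reading errors may not be independent.

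**The 0.50 might be the correlation of baseline with change.** The factor would then be 1 − 0.25 = 0.75, power would still be 80%, and a modest value could fairly be called conservative. This cannot be dismissed on arithmetic alone. But the article says the correlation is in scores, as it does for pain. With equal variances, a stronger baseline–change correlation would also need a score correlation below 0.50, which makes the implied between-person SD smaller still.

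**The primary model adjusts for more than baseline.** The stratifying variables are included, and further models add age, gender, BMI and plateau area. Any gain is unquantified, so 68% is the worst case for a baseline-only model, not a prediction.

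**The practical harm is limited.** The planned 95% confidence intervals will show the precision reached, whatever power was planned, and recruitment has begun. This bears on urgency; it does not make the statement correct.

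**Conclusion.** The point holds as an error of direction. With the SD of change fixed at 3.5%, a score correlation of 0.50 is a favourable assumption, and the stated 80% is not a lower bound. With 115 evaluable per arm, power runs from 80% at ρ = 0.50 through 75% (0.70), 72.5% (0.80) and 70% (0.90) to 68% with no gain from baseline adjustment. With all 144 per arm retained, it is about 77.5–80% for ρ of 0.90 or more.

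This rests on reading 3.5% as the SD of change, which the text supports directly, and on equal variances at the two visits, which is assumed. The 68% floor needs only the first, because baseline adjustment cannot raise the residual variance above that of the change itself. Where in the range the true power lies cannot be settled from the documents. Pain power is above 99% under either variance factor and is not affected.

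**What to change.** Revise the cartilage sentences under Sample size calculations, leaving N = 288 unchanged:

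- Delete the word conservative.
- State that 3.5% is the SD of 12-month percentage change, and give the variance factor (1 + ρ)/2 with its equal-variance assumption.
- Replace the single power figure with a range. Suggested text: With 115 evaluable participants per arm and an SD of percentage change of 3.5%, power to detect a 40% reduction in loss (1.12 percentage points) is 80% if the baseline to 12-month correlation is 0.50, 75% at 0.70, 70% at 0.90 and 68% if baseline adjustment brings no gain; the reduction detectable with 80% power rises accordingly from 40% to about 46%.
- If the source study gives an observed correlation or a between-person SD of cartilage volume, report it so that the reader can place the trial within this range.

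The change costs one paragraph and alters no outcome, test or procedure. The drawback is a less favourable stated power for the structural primary outcome.

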### Statistical analyses

#### Primary analyses

We will conduct an intention-to-treat analysis whereby all participants will be included in the study in the group to which they were randomised. Analysis will be conducted by a biostatistician blinded to treatment group, with two-sided hypothesis tests and *p*-values < 0.05 significant. If the proportion of missing data exceeds 5%, missing outcome data will be imputed using multiple imputation methodology, and sensitivity to the missing at random assumption will be investigated [41]. Changes from baseline will be presented for each group at 2- and 12-month time points using the mean change and 95% confidence intervals. For continuous outcomes (e.g. pain, cartilage volume, physical function), longitudinal analyses will be conducted, with differences in mean change (follow-up minus baseline) compared between the groups using mixed linear regression models with the baseline value, stratifying variables (Kellgren and Lawrence grade and injecting site) and an interaction between month and treatment group as covariates, including random effects for participants [42]. Models including baseline cartilage volume, age, gender, body mass index and cross-sectional area of the medial tibial plateau from MRI [30] will also be fit. Appropriate transformations of outcome measures will be considered if needed to meet statistical assumptions (e.g. linearity, normality and homogeneity of residuals) as assessed using diagnostic plots. Binary outcomes will be compared between groups using risk differences calculated after fitting longitudinal regression models for binary outcomes, adjusted for stratification variables and accounting for clustering of measurements within participants. The other MRI-derived measurements (MOAKS, bone marrow lesion size and cartilage defects) will be compared between groups using appropriate models, adjusting for age, gender, body mass index, and the stratifying variables. The model for cartilage defects will also be adjusted for cross-sectional area of the medial tibial plateau [30]. If appropriate, the effect of PRP on primary outcomes under hypothetical full adherence to assigned treatment will be investigated. The success of blinding will be assessed using the James Blinding Index [43].

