The following secondary outcome measures will also be collected:i)*Average knee pain severity during walking*: measured at baseline, 2 months and 12 months on an 11-point NRS, where 0 indicates no pain and 10 indicates worst pain possible.ii)*Intermittent and Constant Osteoarthritis Pain (ICOAP) questionnaire:* measured at baseline, 2 months and 12 months. This is a self-report multi-dimensional, OA-specific measure of pain experience, with established reliability, internal consistency and validity in people with knee OA [27]. It is comprised of 5-items assessing constant knee pain in the previous week, and 6-items assessing intermittent knee pain in the previous week. Questions regarding pain intensity have terminal responses of ‘not at all’ (score 0) and ‘extremely’ (score 4), and questions regarding pain frequency have ‘never’ (score 0) to ‘very often’ (score 4). Total scores range from 0 to 100, with higher scores indicating worse pain.iii)*Knee Injury and Osteoarthritis Outcome Score:* measured at baseline, 2 months and 12 months. This is a knee-specific self-report outcome measure with high test-retest reliability, internally consistent and face and content validity [28, 29]. Likert responses range from None to Extreme, and scores range from 0 to 100, with lower scores indicating worse symptoms, function or quality of life. It is comprised of the following five subscales:Pain: scored from 9 questions about knee pain frequency experienced in the last week, and the amount of knee pain experienced during specific activities such as twisting, bending and walking.Other symptoms: scored from 7 questions regarding other symptoms experienced in the last week, such as swelling, restricted range of motion and mechanical symptoms.Function in daily living: scored from 17 questions regarding knee function in the last week.Function in sport and recreation: scored from 5 questions regarding function with sport and recreational activities in the last week.Knee-related quality of life: scored from 4 questions about knee-related quality of life experienced in the last week.iv)*Participant-perceived global ratings of change:* participants will rate perceived overall change with treatment (compared to baseline), and change in pain and physical function, on a 7-point Likert scale (from “much worse” to “much better”) at 2 and 12 months [30]. Those ‘moderately better’ or ‘much better’ will be classified as improved. All other respondents will be classified as not improved.v)*Health-related quality of life:* measured at baseline, 2 months and 12 months using the 35-item Assessment of Quality of Life (AQoL-8D) instrument [31]. The AQoL-8D has strong psychometric properties and is more responsive than other widely-used scales [32]. Scores range from − 0.04 to 1.00, with higher scores indicating better quality of life. The AQoL-8D will also be measured at 6 and 9 months for the health economic evaluation.vi)*Other MRI-derived measurements*: using a 3 T whole body system with a dedicated extremity coil and a T1-weighted fat-suppressed 3D gradient recall acquisition sequence (Additional file 1). Outcomes include:MRI osteoarthritis knee score (MOAKS): an OA-specific semi-quantitative tool evaluating multi-feature joint changes associated with OA [33]. We will assess the following subscores: meniscal morphology (any regions with worsening at 12 months compared to baseline; scored as yes or no); inter-condylar synovitis (worsening in inter-condylar synovitis at 12 months compared to baseline; scored as yes or no); cartilage morphology (number of areas with worsening in thickness at 12 months compared to baseline; categorised as 0, 1, 2, or 3+); and whole knee effusion (change in whole knee effusion at 12 months compared to baseline; categorised as worsened, no change or improved).Bone marrow lesion size: assessed from the MRIs at baseline and 12-months using categorical scoring in the medial distal femur and the proximal tibia (range 0–3 per region, with higher scores indicating greater bone marrow lesion size). Progression of bone marrow lesions (yes/no) will be defined as an increase in score by at least 1 from baseline to follow-up in either the medial tibial or medial femoral compartment.Cartilage defects: score in the medial distal femur and the proximal tibia at baseline and 12-months using categorical scoring (range 0–4 per region, with higher scores indicating greater cartilage defects). Progression of medial cartilage defects (yes/no) will be defined as an increase in score by at least 1 from baseline to follow-up in either the medial tibial or medial femoral compartment.

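### The global-rating-of-change outcomes are adjusted for the randomisation strata only; adding baseline pain or function, already collected on everyone, could make the risk differences slightly more precise at no cost

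*Protocol article*

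**What the plan says.** Under Outcome measures, the protocol article defines the global ratings: "participants will rate perceived overall change with treatment (compared to baseline), and change in pain and physical function, on a 7-point Likert scale", at 2 and 12 months. Moderately better or much better counts as improved, and "All other respondents will be classified as not improved". This gives three binary secondary outcomes.

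Under Primary analyses, the plan for these outcomes reads: "Binary outcomes will be compared between groups using risk differences calculated after fitting longitudinal regression models for binary outcomes, adjusted for stratification variables", with allowance for repeated measurements on the same participant. No baseline score is named.

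The same paragraph treats other outcomes differently. Continuous outcomes are analysed with "mixed linear regression models with the baseline value, stratifying variables (Kellgren and Lawrence grade and injecting site"). The other MRI measurements are adjusted for age, gender, body mass index and the strata, and cartilage defects also for tibial plateau area. One further sentence adds models with baseline cartilage volume, age, gender, body mass index and plateau area, but neither baseline pain nor baseline function.

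Both scores exist for everyone. Eligible participants complete the baseline questionnaire before the baseline MRI (Procedures), and allocation is revealed at the first treatment appointment (Randomisation procedures). Average knee pain and the KOOS are both listed as measured at baseline (Outcome measures and Table 1).

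**The concern.** A rating of change from baseline plausibly depends on where the participant started. Someone who enters with more pain has more room to improve. If baseline pain or function predicts the rating, a model that leaves it out treats explainable variation as noise, and the confidence interval for the risk difference is wider than it need be. Chance differences between the arms in baseline severity also stay in the point estimate. The interval allows for them, but adjustment would remove part of them.

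What is at stake is a little precision on three patient-reported secondary outcomes named in the secondary aim. If adjustment is wanted, it is best named before the data are seen, because a covariate added afterwards invites the charge that it was chosen for its result.

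**Working it through.** **1. The plan's own figures.** The protocol gives no sample size or power for the global ratings. Its cartilage calculation supplies the number per arm used below.

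- Inputs (Sample size calculations): control loss 2.8%, SD 3.5%, 40% reduction, baseline correlation 0.50, two-sided 0.05, 80% power, 20% loss to follow-up.
- Difference: 0.40 × 2.8 = 1.12.
- Without covariate adjustment: 2 × [3.5 × (1.960 + 0.842) / 1.12]² = 153.3 per arm.
- Analysis of covariance: 153.3 × (1 − 0.50²) = 115 per arm.
- With loss to follow-up: 115 / 0.80 = 143.75, so 144 per arm and 288 in all.

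The stated figures reproduce.

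**2. Effect of adding one baseline score to the binary model.** The correlation between a baseline score and a global rating is not in the protocol, and neither are the proportions improved. Both are assumed here.

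- Design: 115 per arm, one time point, 3,000 simulated trials per scenario, strata left out of both analyses.
- Outcome: a normal latent score, correlated with the baseline score, is cut to give the stated proportion improved.
- Proportions improved: 40% v 40%, 40% v 55% and 30% v 45%.
- Comparison: the simple risk difference against the risk difference standardised from a logistic model with treatment and the baseline score.
- SE change: square root of the variance ratio, minus 1. For example, at correlation 0.29 the variance ratio is 0.943 to 0.957, and √0.943 − 1 = −2.9%, √0.957 − 1 = −2.2%.

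| Assumed latent correlation | Variance ratio, adjusted / unadjusted (range over the three settings) | Change in SE | 95% CI half-width, 40% v 55% | Power, 40% v 55% |
|---|---|---|---|---|
| 0 | 1.004 to 1.006 | +0.2 to +0.3% | 0.127 → 0.128 | 64% → 63% |
| 0.1 | 0.993 to 0.997 | −0.2 to −0.4% | 0.127 → 0.126 | 64% → 64% |
| 0.2 | 0.972 to 0.980 | −1.0 to −1.4% | 0.126 → 0.124 | 65% → 66% |
| 0.29 | 0.943 to 0.957 | −2.2 to −2.9% | 0.128 → 0.125 | 63% → 66% |
| 0.4 | 0.896 to 0.923 | −3.9 to −5.4% | 0.127 → 0.122 | 64% → 68% |
| 0.5 | 0.833 to 0.862 | −7.1 to −8.7% | 0.127 → 0.117 | 64% → 71% |

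Check on the unadjusted SE: √[(0.40 × 0.60 + 0.55 × 0.45) / 115] = 0.065, half-width 1.96 × 0.065 = 0.128, as simulated. The small differences between rows in the unadjusted columns are simulation noise. The mean risk difference is the same with and without adjustment, to within about 0.001.

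**3. What the protocol's pain figures say about the correlation.** The protocol gives "standard deviation (SD) of change in pain of 2.4 and baseline to 12-month correlation in scores of 0.29". Write r = 0.29, S₁ for the baseline SD and S₂ for the 12-month SD. Then S₁² + S₂² − 2rS₁S₂ = 2.4², and the correlation of change with baseline is (rS₂ − S₁) / 2.4. The protocol does not give S₁, so it is assumed:

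| Assumed baseline SD | Implied 12-month SD | Correlation of change with baseline |
|---|---|---|
| 1.2 | 2.46 | −0.20 |
| 1.4 | 2.40 | −0.29 |
| 1.6 | 2.31 | −0.39 |
| 2.01 (equal SDs) | 2.01 | −0.60 |

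These are correlations for the calculated change in NRS pain. A participant's own rating of change is a different measure, and the protocol does not link the two.

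**The case against.** The strongest objection is that nothing here is an error. Adjusting for the randomisation strata gives a valid risk difference. The rule for continuous outcomes uses each outcome's own baseline value, and a global rating of change has none, so leaving one out is consistent. Pain and function are also analysed as continuous outcomes with baseline adjustment, so the secondary aim does not rest on these ratings for its precision. All of this stands, and it limits the point to an optional improvement. It does not remove the point. The covariate set is stated rather than left open, and a rating without its own baseline can still be adjusted for baseline pain or function.

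A reader might infer three stronger things that the protocol does not support:

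- **That the protocol's figures make change in pain correlate −0.60 with baseline, so the gain must be large.** That value requires equal SDs at baseline and 12 months, which the protocol does not state. The entry rule of at least 4 on the NRS restricts the baseline range but not the follow-up range, which makes equal SDs doubtful. Baseline SDs of 1.2 to 1.6 give −0.20 to −0.39.
- **That chance baseline imbalance makes the planned analysis wrong.** Under randomisation the confidence interval already allows for it.
- **That 2- and 12-month effects will not be separated, because the binary sentence lists no month-by-group term.** The models are described as longitudinal, the ratings are taken at 2 and 12 months, and the secondary aim asks for both. This is the brevity of an article.

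**Conclusion.** The point holds as a small, free gain in precision on three secondary outcomes. The planned risk differences are valid; what can be improved is their standard error.

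The size depends on a correlation that the protocol does not report. Over assumed values from 0 to 0.5, the change in standard error runs from about zero to a reduction of 7 to 9%. Values of 0.2 to 0.29 give a reduction of about 1 to 3%. If the ratings mainly reflect how participants feel on the day and are unrelated to baseline, nothing is gained and about 0.5% of variance is lost. The possible gain is therefore much larger than the possible loss, but a worthwhile gain is not assured.

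These figures rest on 115 evaluable participants per arm, one covariate, one time point and the assumed proportions improved.

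**What to change.** In the binary-outcome sentence of the Primary analyses section, add *and baseline score* after the stratification variables, and name the score for each rating:

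- baseline average knee pain (NRS) for the overall and pain ratings;
- baseline KOOS function in daily living for the physical function rating.

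State that the risk difference is obtained by marginal standardisation, that is, by averaging predicted probabilities over all participants under each allocation. It then stays a population risk difference with the planned interpretation.

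The cost is one amended sentence, made before unblinding, in the protocol or in the statistical analysis plan. No new data, participants or visits are needed, and the sample size does not change.

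### The covariate list for the MOAKS, bone marrow lesion and cartilage-defect outcomes omits the baseline score of the same feature, at a modest cost in precision and protection against chance imbalance

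*Protocol article*

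**What the plan says.** The Primary analyses section of the protocol article treats these outcomes in one sentence. It begins "The other MRI-derived measurements (MOAKS, bone marrow lesion size and cartilage defects" and says they "will be compared between groups using appropriate models, adjusting for age, gender, body mass index, and the stratifying variables". One outcome-specific addition follows: "The model for cartilage defects will also be adjusted for cross-sectional area of the medial tibial plateau". The type of model is left open, but the covariates are named.

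In the same section, continuous outcomes are analysed with "mixed linear regression models with the baseline value, stratifying variables (Kellgren and Lawrence grade and injecting site", among other terms. The sentence that brings in baseline cartilage volume follows those continuous models and does not extend to the scored MRI features.

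Outcome measures defines all the scored features as change from baseline:
- "Progression of bone marrow lesions (yes/no) will be defined as an increase in score by at least 1" in either medial region. Cartilage defects follow the same rule.
- Effusion is "categorised as worsened, no change or improved".
- Meniscal morphology and synovitis are worsening yes or no.
- MOAKS cartilage morphology is a count of worsened areas.

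The lesion scale is "range 0–3 per region, with higher scores indicating greater bone marrow lesion size" and the defect scale is "range 0–4 per region, with higher scores indicating greater cartilage defects".

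**The concern.** When an outcome is a step up a short bounded scale, the starting grade partly determines it. A region already at its maximum cannot progress, and a knee with no effusion cannot improve. Baseline grade can therefore be prognostic, and it is already read from the baseline MRI.

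The only severity variable in the list is Kellgren and Lawrence grade. It is an x-ray grade limited by eligibility to 2 or 3, and it does not directly measure marrow lesions, synovitis or effusion. Baseline lesion load is not a stratification factor either.

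Two things are at stake for these secondary outcomes: some avoidable loss of precision, and estimates that move with whatever imbalance in baseline score the randomisation happens to produce. If such an imbalance is noticed after unblinding, adding the covariate at that point would be post hoc, and leaving it out would cloud the result.

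**Working it through.** **Step 1. The plan's own figures.** Inputs from Sample size calculations: control loss 2.8%, SD 3.5%, 40% reduction, correlation 0.50, two-sided 5%, power 80%, 20% loss to follow-up.
- Difference = 0.4 × 2.8 = 1.12.
- n per arm without baseline adjustment = 2 × [3.5 × (1.960 + 0.842) / 1.12]² = 153.3.
- With adjustment: 153.3 × (1 − 0.50²) = 114.97, so 115 per arm, as stated.
- 115 / 0.8 = 143.75, so 144 per arm and 288 in total, as stated.

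The sample size rests on cartilage volume, which is already baseline-adjusted. Nothing below alters it.

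**Step 2. Effect of omitting baseline on yes/no progression.** The article gives no baseline score distributions and no progression risks, so these are assumed. The set-up was:
- 115 per arm and two correlated medial regions.
- Progression if either region rises, and zero risk in a region at its maximum.
- 1,500 simulated trials per scenario, with no treatment effect or with a regional odds ratio of 0.45.
- Logistic models with treatment group alone, or with group plus the sum of the two baseline grades and its square. Risk differences were standardised.

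| Scenario | Baseline grades, % (lowest to highest) | Regional control risk by grade, % | Control progression | Variance ratio, no effect / effect | Power without → with baseline |
|---|---|---|---|---|---|
| Lesion A | 40/30/20/10 | 15/20/20/0 | 29% | 0.999 / 1.002 | 74.7% → 75.8% |
| Lesion B | 40/25/20/15 | 10/30/40/0 | 35% | 0.911 / 0.943 | 74.0% → 76.4% |
| Lesion C | 60/20/15/5 | 8/30/35/0 | 29% | 0.927 / 0.939 | 65.5% → 69.3% |
| Defect A | 10/20/35/25/10 | 15/20/25/20/0 | 35% | 0.985 / 0.988 | 77.3% → 79.4% |
| Defect B | 5/15/25/30/25 | 30/35/30/20/0 | 36% | 0.889 / 0.920 | 74.0% → 76.8% |
| Defect C | 5/10/15/30/40 | 40/40/35/25/0 | 33% | 0.793 / 0.845 | 65.9% → 74.9% |

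- Variance reduction: from nil (Lesion A) to 1 − 0.793 = 21% (Defect C, no effect).
- Power gain: from 75.8 − 74.7 = 1.1 points to 74.9 − 65.9 = 9.0 points.
- Type I error: 3.9% to 5.3% without baseline and 4.1% to 5.7% with it. Simulation error at 5% is √(0.05 × 0.95 / 1500) = 0.6 points.
- Mean risk difference: the same to within 0.001 in every scenario.

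**Step 3. Chance imbalance.** Imbalance is the between-arm difference in mean baseline sum. With no treatment effect, its correlation with the unadjusted risk difference is −0.07, 0.05 and 0.20 for Lesion A to C, and −0.09, −0.33 and −0.45 for Defect A to C. In Defect C, an imbalance of one SD (its SD across simulated trials) shifts the estimate by 2.8 percentage points. With the baseline term, the correlations are about zero.

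**Step 4. Three-category outcome.** Only effusion has this form. A separate illustration used a single assumed 0–3 score at 115 per arm. Baseline categories cut the standard error by about 7%, and power rose from 40% to 47% or from 67% to 73% at two effect sizes. For yes/no worsening on that score, power rose from 32% to 34% or from 55% to 58%. Control risks of worsening there were 41%, 42%, 32% and 0% at grades 0 to 3, so the relation with baseline is not a straight line.

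**The case against.** The strongest reply is that nothing in the plan is invalid. Under 1:1 randomisation, leaving out a prognostic covariate does not bias the comparison, and its standard error already allows for chance imbalance. That stands. A reader might infer from the bounded scales that these comparisons are biased or the error rate inflated; the results above show neither.

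A reader might also infer that every structural secondary outcome loses precision, or that a region at its maximum rules out progression. Neither follows:
- The gain is about nil when few knees sit near a bound. The upper end needs about 40% of regions at the ceiling, which the article does not support.
- Progression counts in either of two regions, so it is impossible only when both are at maximum. In Defect C that would be 16% of knees if the regions were independent (0.4 × 0.4), and at most 40% if they were fully tied.
- Only effusion can be scored as improved, and the article gives no numeric bounds for the MOAKS items.

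It can be said that the general rule for binary outcomes adjusts only for the stratification variables, so this list is already the longer one. That carries less weight: the participant global ratings, the evident use of that rule, have no baseline value to adjust for.

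Finally, an analysis plan that is not shown could add the term. That is possible, but the article states a list, down to one outcome-specific covariate, and does not simply leave the matter open.

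**Conclusion.** The point holds as a minor one, on secondary outcomes only. The plan names covariates for these models and omits the baseline score of the same feature, without giving a reason and unlike its treatment of continuous outcomes. The cost is precision and exposure to chance imbalance: about 0% to 21% of the variance of the risk difference, or 1 to 9 power points.

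That range rests on assumed baseline distributions, progression risks and one effect size. The simulated models contained no Kellgren and Lawrence grade, age, gender or body mass index, so the net gain on top of the planned covariates may be smaller. The smallest power gains are of the order of the simulation error of a single rate, √(0.75 × 0.25 / 1500) = 1.1 points, although both analyses used the same simulated data. The MOAKS cartilage morphology count was not simulated.

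The primary outcomes, the sample size and the validity of the tests are unaffected.

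**What to change.** Add one parsimonious baseline term for the same feature to each of these models, fixed before the analyst is unblinded:
- Bone marrow lesions and cartilage defects: the sum of the medial tibial and medial femoral baseline grades, linear or with a quadratic term, since the risk can rise and then drop to zero at the ceiling.
- Effusion and synovitis: the baseline grade.
- Meniscal and cartilage morphology: one summary baseline score, defined in advance.

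Report standardised risk differences for the yes/no outcomes. The plan already uses risk differences for binary outcomes, and standardising keeps the estimate on the same scale with or without the added covariate. If the baseline score is left out on purpose, state why.

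The data are already collected, so the cost is a sentence or two of model wording. The small downside is sparse categories at about 115 per arm. Full sets of regional category indicators should be avoided, because a grade with zero possible progression produces separation in a logistic model.
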